## Abstract

**Background:**

Major depressive disorder (MDD) is a considerable public health concern. In spite of evidence-based treatments for MDD, many patients do not improve and relapse is common. Therefore, improving treatment outcomes is much needed and adjunct exercise treatment may have great potential. Exercise was shown to be effective as monotherapy for depression and as augmentation strategy, with evidence for increasing neuroplasticity. Data on the cost-effectiveness and the long-term effects of adjunct exercise treatment are missing. Similarly, the cognitive pathways toward remission are not well understood.

**Methods:**

The present study is designed as a multicenter randomized superiority trial in two parallel groups with follow-up assessments up to 15 months. Currently depressed outpatients (*N* = 120) are randomized to guideline concordant Standard Care (gcSC) alone or gcSC with adjunct exercise treatment for 12 weeks. Randomization is stratified by gender and setting, using a four, six, and eight block design. Exercise treatment is offered in accordance with the NICE guidelines and empirical evidence, consisting of one supervised and two at-home exercise sessions per week at moderate intensity. We expect that gcSC with adjunct exercise treatment is more (cost-)effective in decreasing depressive symptoms compared to gcSC alone. Moreover, we will investigate the effect of adjunct exercise treatment on other health-related outcomes (i.e. functioning, fitness, physical activity, health-related quality of life, and motivation and energy). In addition, the mechanisms of change will be studied by exploring any change in rumination, self-esteem, and memory bias as possible mediators between exercise treatment and depression outcomes.

**Discussion:**

The present trial aims to inform the scientific and clinical community about the (cost-)effectiveness and psychosocial mechanisms of change of adjunct exercise treatment when implemented in the mental health service setting. Results of the present study may improve treatment outcomes in MDD and facilitate implementation of prescriptive exercise treatment in outpatient settings.

**Trial registration:**

This trial is registered within the Netherlands Trial Register (code: NL8432, date: 6th March, 2020).

## Background

Around 268 million people worldwide suffer from major depressive disorder (MDD), indicating that depression is a highly prevalent condition [1]. Those affected experience persistent feelings of sadness and a loss of pleasure or interest in activities. Physical comorbidities such as cardiovascular diseases [2] and metabolic risk factors [3] are common too and MDD is one of the leading causes of disability and mortality worldwide [4]. Moreover, MDD is not just a burden for the individual, but also impacting the society as a whole. For example, incremental costs of patients suffering from MDD have been estimated at $210 billion in the United States [5]. Given the high prevalence and personal and societal burden, improving treatment of MDD is essential.

Standard treatment options consist of antidepressant medication and/or psychological interventions such as cognitive behavior therapy (CBT) and interpersonal therapy (IPT). While those treatment options are overall effective and generally of comparable effectiveness [6], approximately 40% of depressed patients do not respond adequately to treatment [7, 8] and recurrence rates are high (i.e. greater than 60%) [9]. Importantly, most treatment options have disadvantages, including high costs and unpleasant side effects. Moreover, they have no direct effect on somatic risk factors and comorbid somatic diseases. Hence, there is a need for new (combination) treatments.

One such treatment option is physical exercise. Exercise has been shown to be effective as monotherapy [10–13] and as augmentation strategy for antidepressant medication and psychological treatment [14–19]. Previous research showed that especially the combination of exercise and another treatment (i.e. antidepressants or psychological intervention) is effective in reducing depressive symptoms [19, 20]. Further, exercise may prevent relapse [21], benefits physical comorbidities [22], and is - unlike other treatments for depression - inexpensive, universally accessible, and shows favourable tolerability [23]. Hence, implementing an evidence-based exercise treatment module within depression standard care seems feasible and is hypothesized to be (cost-)effective. Nonetheless, the long-term effects of exercise treatment are largely unexplored [24, 25]. Therefore, the first aim of the present study is to investigate the (cost-)effectiveness of exercise as adjunct treatment for depression within the mental health system, including examination of the long-term effects up to 15 months.

Furthermore, exercise might not only improve depression but might benefit other health outcomes as well. For instance, regular exercise leads to improved fitness [26, 27] and several studies showed that exercise programs increase overall physical activity levels [28–30]. Similarly, exercise interventions are used to improve physical functioning in the elderly [31] and to counteract fatigue in somatic patients [32]. These positive effects can also be expected in depressed individuals engaging in regular exercise [33, 34]. Therefore, the second aim of this study is to examine the effect of exercise treatment on additional (mental) health outcomes, focusing on fitness, physical activity, health-related quality of life, disability, and motivation and energy.

Most research has focused on the effectiveness of exercise treatment for depression, with increasing but still limited attention for its mechanisms of change. Recently, Kandola and colleagues [35] reviewed evidence for the biological and psychosocial working mechanisms of physical activity and exercise specifically. They report evidence for increased neuroplasticity, especially in the hippocampus which is relevant to cognitive emotional processing and memory functions [35–37]. The psychosocial mechanisms are less well understood, with some research pointing toward self-esteem, social support, and self-efficacy [35, 38]. The authors therefore conclude that especially research on cognitive and psychosocial mechanisms is desirable. Knowing how an intervention works is essential to improving intervention techniques. Therefore, the third aim of the present study is to investigate cognitive and psychosocial mechanisms of change, focusing on rumination, self-esteem, and memory bias.

Rumination is a common symptom of depression and associated with its onset, maintenance, and recurrence [39]. Studies showed that exercise not only affects depressive symptoms in general, but also decreases rumination [40, 41]. Those studies indicate that rumination may mediate the effect of exercise on depressive symptoms. Moreover, exercise increases self-esteem and initial findings suggest that self-esteem mediates the relation between exercise and depression [35]. We aim to replicate the evidence for rumination and self-esteem as possible mechanisms of change. In addition, we examine memory bias as potential mediator which is related to rumination [42, 43] and self-esteem [44]. Negative bias in recall of self-related information has been recognized as important factor in the development and maintenance of depression (see cognitive model by Beck) [45–49]. As previous research identified that neuroplasticity in the hippocampal circuit increases through exercise which is linked to memory bias [50], changes in this circuit may allow depressed individuals to process emotional information differently, possibly decreasing the automatic preferential recall of negative information and in turn depressive symptoms. In summary, the aim of the present study is threefold: 1) we will investigate the long-term (cost-)effectiveness of adjunct exercise treatment and 2) its effect on additional positive outcomes as well as, 3) possible mechanism of change, focusing on rumination, self-esteem, and memory bias.

## Methods

### Study design

In this pragmatic superiority trial, patients are randomly assigned to either gcSC or the exercise intervention adjunct to gcSC. Measurements take place at baseline (T0), after session 3 (after 3 exercise sessions or 3 weeks of gcSC alone; T1), 6 (T2), 9 (T3) and 12 (T4), and 6 (T5), 9 (T6), 12 (T7), and 15 (T8) months post-baseline. Patients in the gcSC condition can receive the adjunct exercise intervention after completion of the follow-up assessments.

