**Fig. 1 Fig1:**
[figure not shown]
CONSORT flow chart

Patients in the gcSC with adjunct exercise condition start the exercise treatment simultaneously to the gcSC treatment (with a maximum two-week difference between start dates). Patients complete the baseline assessment in the week before the first treatment session. The surveys are sent via email using the online cloud-based data solution program, Castor EDC and can be filled out via any personal device (e.g. computer, tablet). This program is also used for the Case Report Forms and initial data management. Additionally, patients receiving the adjunct exercise treatment fill out a short questionnaire before and after each supervised exercise session on paper, as part of the treatment. An overview of the assessments can be found in Table 1 and Fig. 1. Expected study duration is 36 months. Inclusion of patients started in March 2020.

**Table 1 Tab1:** Assessment schedule

		Time point								
Endpoints	Material	T0	T1	T2	T3	T4	T5	T6	T7	T8
Primary outcome	IDS-SR	X	X	X	X	X	X	X	X	X
Secondary outcomes	SCID-5-S					X	X	X	X	X
	IPAQ	X	X	X	X	X	X	X	X	X
	Fitness^a^	X				X				
	WHODAS	X				X				X
	MEI-SF	X				X				X
Economic evaluation	EQ-5D-5L	X				X	X	X	X	X
	Tic-P	X				X	X	X	X	X
Mechanisms	RRS	X	X	X	X	X	X	X	X	X
	RSES	X	X	X	X	X	X	X	X	X
	SRET	X				X				X

^a^Assessed in 15% of randomly selected patients from both conditions

*IDS-SR* Inventory of Depressive Symptomatology (i.e. depressive symptoms)*, SCID-5-S* Structured Clinical Interview for DSM-5 (i.e. depressive remission), *IPAQ* International Physical Activity Questionnaire (i.e. physical activity), *WHODAS* World Health Organization Disability Assessment Schedule (i.e. disability), *MEI-SF* Motivation and Energy Inventory-Short Form (i.e. motivation and energy), *EQ-5D-5L* (i.e. quality of health), *Tic-P* Trimbos Institute and iMTA Cost questionnaire for Psychiatry (i.e. economic costs), *RRS* Ruminative Response Scale (i.e. rumination), *RSES* Rosenberg Self-Esteem Scale (i.e. self-esteem), *SRET* Self-Referent Encoding Task (i.e. memory bias)

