#### Adjunct exercise

Patients receiving the adjunct exercise treatment, exercise once a week under supervision of psychomotor therapists or trained nurses and commit to exercising twice a week at home for 12 weeks. Supervised exercise generally consists of running or indoor cycling (spinning), which are usually both offered in a group setting, although other exercise types and individual supervised exercise are also provided. The exercise sessions last for 45 min at moderate intensity, which is based on heart rate frequency (i.e. *moderate = 64–76% of HRmax = 220 – age)*. This kind of exercise intervention is evidence-based and recommended by the National Institute for Health and Care Excellence (NICE) [61]. Patients track the intensity, duration, and frequency of each exercise session, with the aid of a non-invasive activity tracker (Fitbit)^3^ which is provided for the length of the study (i.e. 15 months).

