#### Physical activity and fitness

To assess self-rated physical activity level, the Dutch version of the International Physical Activity Questionnaire (IPAQ) [65] is used. Psychometric properties of this questionnaire were shown to be acceptable in different settings and populations [66]. Moreover, to assess objective physical activity level and heart rate, patients receive the Fitbit in the adjunct exercise intervention condition, as it allows self-dosing during the exercise sessions, enables patients to learn how to effectively exercise to counteract depression, and helps patients motivate themselves, hence contributing to adherence. Additionally, to objectively assess physical fitness, fitness tests will be conducted at baseline and after the 12 weeks of exercise or gcSC treatment in 15% of the sample (selected at random). Here, the main endpoint is improvement in cardiorespiratory fitness.

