### Statistical analysis

Given the ongoing advances in statistics and technology, all analyses will be performed in line with best current practice. Following the CONSORT statement [78], all our analyses will adhere to the intention-to-treat (ITT) principle (i.e., with an analysis of all patients as randomized). To this end, analyses of treatment effects will be conducted with multilevel mixed modelling, with treatment condition as factor and the depended measure as baseline covariate, while missing observations will be multiply imputed (with chained equations) for the health-economic analyses. In addition, we will also report the results in the per-protocol sample (≥ 6 supervised exercise sessions). Generalized (logit) mixed modelling will be used to compare the conditions on number of patients in remission at each follow-up measure. To examine whether rumination, self-esteem and memory bias are the mechanisms of change between adjunct exercise treatment and a decrease in depressive symptoms, multilevel structural equations modelling will be performed in Stata [79], or alternatively Hayes’ PROCESS macro [80] for SPSS [81] will be used.

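### T1–T4 follow exercise sessions in one arm and calendar weeks in the other; read literally, any missed session makes T4 late or leaves it without a trigger in the exercise arm only

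*Protocol article*

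**What the plan says.** The Study design section schedules T1 to T4 "after session 3 (after 3 exercise sessions or 3 weeks of gcSC alone; T1), 6 (T2), 9 (T3) and 12 (T4". The unit is sessions in the exercise arm. In the control arm it is weeks of gcSC, stated for T1 and carried on by the same count to T2–T4. The same sentence then puts the later assessments at "6 (T5), 9 (T6), 12 (T7), and 15 (T8) months post-baseline", one calendar clock for both arms.

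Four other places bear on this:

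- **Adjunct exercise:** patients "exercise once a week under supervision of psychomotor therapists or trained nurses and commit to exercising twice a week at home for 12 weeks". That is one supervised session a week, 12 in all, and three sessions a week if home sessions count.
- **Physical activity and fitness:** "fitness tests will be conducted at baseline and after the 12 weeks of exercise or gcSC treatment". Table 1 gives this test at T0 and T4 only, so here T4 is worded in weeks for both arms.
- **Statistical analysis:** the analysis is by intention to treat, "with an analysis of all patients as randomized", and "we will also report the results in the per-protocol sample (≥ 6 supervised exercise sessions". Patients with as few as half the planned supervised sessions are thus foreseen, and those with fewer stay in the main analysis.
- **Procedure (text after Fig. 1):** exercise patients "start the exercise treatment simultaneously to the gcSC treatment (with a maximum two-week difference between start dates". Baseline is completed in the week before the first treatment session.

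**The concern.** When a visit is reached through attendance in one arm and through the calendar in the other, time since baseline at that visit depends on behaviour after randomisation in one arm only. A comparison at T4 may then set patients at different distances from baseline side by side, or it may lack T4 selectively for poor attenders in the exercise arm. Either outcome sits badly with an analysis of everyone as randomised.

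T4 carries much of the trial. In Table 1 every instrument is scheduled there. It holds the end-of-treatment IDS-SR, the first SCID remission rating, the only post-baseline fitness test, and the first post-baseline WHODAS, MEI-SF, SRET, EQ-5D-5L and Tic-P. The IDS-SR and the rumination and self-esteem measures at T1–T3 follow the same rule, and the mediation aim draws on them. QALYs weight utility by time spent in a state, so a T4 of uncertain date also affects that calculation.

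**Working it through.** **Inputs from the article.** One supervised session a week for 12 weeks; triggers at sessions 3, 6, 9 and 12 (exercise) or weeks 3, 6, 9 and 12 (control); T5 at 6 months, about week 26.

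**Assumed input.** Attendance a, the chance that a weekly supervised session is attended, taken as independent from week to week. The article gives no value, so a range is shown.

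**Step 1. The plan's own equivalence.** With a = 1, session k falls in week k. T1–T4 are then at weeks 3, 6, 9 and 12 in both arms and the gap is zero.

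**Step 2. Missed sessions made up until 12 are reached.** The expected week of session k is k/a. For T4 this is 12/a. The chance of having 12 sessions by week 12 is a^12.

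| Attendance a | Expected week of T4, exercise arm (12/a) | T4, control arm | Lag (weeks) | Chance of 12 sessions by week 12 (a^12) |
|---|---|---|---|---|
| 100% | 12.0 | 12 | 0 | 100% |
| 90% | 13.3 | 12 | 1.3 | 28% |
| 80% | 15.0 | 12 | 3.0 | 7% |
| 70% | 17.1 | 12 | 5.1 | 1.4% |
| 60% | 20.0 | 12 | 8.0 | 0.2% |
| 50% | 24.0 | 12 | 12.0 | under 0.1% |

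The earlier visits drift in the same way. At 80% the expected weeks for T1–T3 are 3/0.8 = 3.75, 6/0.8 = 7.5 and 9/0.8 = 11.25. The 50% row matches 6 of 12 sessions, the per-protocol minimum. There T4 would almost meet T5, and about 28% of such patients would not have reached session 12 by week 26 (binomial: chance of at least 12 attended in 26 is 0.721).

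**Step 3. Programme ends at 12 weeks with no make-up.** No lag arises at T4. Instead, anyone who misses one session never reaches session 12, so the last column becomes the share with a defined T4: 28% at 90% attendance and 7% at 80%. Steps 2 and 3 are mutually exclusive readings and must not be added together.

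**Step 4. Which sessions count.** If all three weekly sessions were counted, triggers at 3, 6, 9 and 12 sessions would fall at weeks 1, 2, 3 and 4. The pairing with 3 weeks of gcSC makes the supervised session the natural unit, but the text does not say so.

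**Step 5. The two wordings of T4.** Study design gives session 12 for the exercise arm; Physical activity and fitness gives 12 weeks for both arms. They agree only when a = 1.

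**The case against.** The strongest reply is that a nominal schedule was meant. Study design treats three sessions and three weeks as equivalent, the programme is one supervised session a week for 12 weeks, and the fitness wording fits that reading. The article never says that sessions must be attended to count. Surveys are emailed through the EDC system, separately from the paper forms tied to each supervised session, and nothing says that assessment stops when exercise stops. Windows and trigger rules are also details that an article may leave to the full protocol.

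Much of this stands. Attendance as the trigger is an inference, though the natural one, and a nominal calendar may be what happens in practice. What does not fall away is that the published rule names two different units for the two arms, while the same sentence uses a common clock from T5 on. This is a rule fixed badly, which goes beyond a missing detail.

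A reader might also infer a quantified bias in favour of exercise. For example, an assumed 0.3 to 0.6 IDS-SR points of improvement per extra week and an assumed SD of 12 turn a lag of 3 to 5 weeks into 0.9 to 3.0 points, or 0.08 to 0.25 SD. The document does not support this: attendance, weekly slope and SD are all absent from it, and so is any statement that missed sessions are made up. Nor does the two-week allowance between start dates show a delay in exercise-arm assessments, because it has no stated direction.

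**Conclusion.** The point holds as a flaw in the timing rule for T1–T4. Taken literally, the rule makes either the date of T4 or its existence depend on attendance in one arm only. Under make-up sessions the expected lag at T4 is 12/a − 12 weeks, so 1.3 weeks at 90% and 3.0 at 80%. Without make-up sessions there is no lag, but patients who miss a session have no T4 trigger. Both results rest on assumed attendance and on supervised sessions being the ones counted.

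The limits are equally clear. The gap is zero at full weekly attendance. T5–T8 are on calendar time and unaffected, so the long-term IDS-SR comparisons are not exposed. If a nominal weekly schedule is already in use, the remedy is a correction of wording. The size of any effect on the IDS-SR comparison is unknown.

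**What to change.** - Define T1–T4 in both arms as 3, 6, 9 and 12 weeks after T0, with one common window. T0 is the clock already used for T5–T8. Randomisation is a poorer anchor: it follows consent, while baseline falls in the week before first treatment, and the interval between the two is not stated.
- Send the surveys and arrange the T4 interview and tests on that clock, regardless of sessions attended or of stopping exercise.
- Bring the Study design and the Physical activity and fitness sections into line on T4.
- For patients already assessed on a session trigger, add a sensitivity analysis using actual weeks since T0.

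The cost is a change of wording and of survey-trigger settings in the EDC system, plus one extra analysis. The exercise programme is not touched. The downside is that some slow attenders will be measured before completing 12 sessions, which is consistent with the planned intention-to-treat analysis.

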### Aims and hypotheses

The primary aim of the study is to evaluate the (cost-)effectiveness of exercise as adjunct treatment for depression in a randomized controlled trial (RCT). We expect that gcSC with the adjunct exercise intervention is more effective and cost-effective than gcSC alone in reducing depressive symptoms in outpatients with MDD, treated in Dutch specialised mental health services.The second aim is to assess the effect of adjunct exercise treatment on physical activity, fitness, health-related quality of life, disability and motivation and energy. We hypothesize that gcSC plus adjunct exercise outperforms gcSC alone on these outcomes.The third aim is to examine putative cognitive mechanisms of change. We expect that a reduction in ruminative thinking style, as well as, an increase in self-esteem and a decline in negative memory bias mediate the between-group effects on depression symptom severity.

### Participants

We will include 120 adult outpatients diagnosed with MDD, according to the Diagnostic and Statistical Manual of Mental Disorders [51]. Exclusion criteria are: Below the age of 16, lifetime manic episode, current psychosis, chronic depression (i.e. current depressive episode > 2 years), dysthymic disorder, high health risks of physical activity based on the screening tool Physical Activity Risk Questionnaire (PAR-Q) [52], insufficient comprehension of the Dutch language to fill out the questionnaires, and physical, cognitive, or intellectual impairments interfering with participation or informed consent.

### Sample size calculation

A recent meta-analysis on the effectiveness of exercise interventions compared to non-exercise comparators in adult outpatients with MDD [10] reports an overall medium to large effect on depressive symptoms, with Hedges’s g = 0.79. This meta-analysis included 11 trials, investigating both exercise as adjunct treatment to gcSC and exercise as monotherapy for depression. In order to provide the most optimal effect size estimate, we conducted our own meta-analysis, including only the trials examining the augmenting effect of exercise, to synthesize the available evidence from the most comparable trials. We identified four studies (moderate/high level of evidence; GRADE) [53] with similar designs to the present RCT that evaluated aerobic exercise as adjunct to gcSC in unipolar depressed mental health care outpatients, with depressive symptom levels as outcome [54–57]. The meta-analysis yielded a Hedge’s g effect size of 0.98 (95%CI = 0.51 ~ 1.45), se = 0.26, *t* = 3.84, *p* = .032, with only moderate heterogeneity, I^2^ = 37%. One study by Rueter and colleagues [56] appeared an outlier (based on the Galbraith plot). When removing this study to account for variations across studies, heterogeneity disappeared with I^2^ = 0%, while the effect size was similar to the original meta-analysis, including 11 trials (g = 0.79; 95%CI 0.42 ~ 1.17; se = 0.190; *p* = .053). Based on the latter, we assumed a between-group effect size of g = 0.70 for the power analysis.

The power calculation was based on guidelines offered by Hemming et al. [58] and accounted for the hierarchical data structure with patients being clustered in psychomotor therapists with a mean cluster size of *N* = 10 (range 5 ~ 15) [59] and an intra-cluster correlation of 0.05 [60], which introduces a design effect of 1.48. In addition, we assumed a correlation between baseline depressive symptoms and the relevant follow-up of *r* = 0.30 for the planned baseline-adjusted multilevel mixed analysis. In order to be able to detect an effect size g ≥ 0.70 as statistically significant at α < 0.05 (two-sided) with a power of (1-β) = 0.80, power analyses revealed a required minimum *N* = 60 per arm (*N* = 120 in total).

